### Study design

This is a two-arm parallel cluster randomized study comparing two models of care for TB contact investigation and management. This study contains three phases:
Baseline phase (phase I) in which retrospective data collection and register quality checks were done in order to assess if the facility registers could be a reliable source of documents for the study. During this phase, there was also a baseline qualitative assessment with adult TB patients who are parents and stakeholders to better prepare the intervention phase and assess the acceptability and feasibility of the proposed activities.Intervention phase (phase II) includes implementation and participant recruitment in the two models of care and study data collection.Explanatory phase (phase III) contains the endpoint analysis and reporting, a cost-effectiveness analysis, and a post-intervention qualitative assessment with adult TB patients who are parents and cluster stakeholders to collect the acceptability of the implemented package.

This research is known under the name of CONTACT study (Community Intervention for Tuberculosis Active Contact Tracing and Preventive Therapy) and represents a research project embedded in a multi-country pediatric TB implementation program called Catalyzing Pediatric TB Innovations (CaP TB) led by the Elizabeth Glaser Pediatric AIDS Foundation (EGPAF) and funded by Unitaid.

### Study setting

This study is conducted in two high TB incidence, resource-limited African countries: Cameroon located in West Africa and Uganda in East Africa, with important differences in programmatic delivery of TB services. In Cameroon, TB care and management is centralized. Only secondary-level health facilities have TB laboratory diagnostic facilities and TB patients can only access care and drugs from these health facilities. In Uganda, TB management is decentralized to the primary healthcare level. In both countries, national guidelines [28, 29] at the time of this study development recommended contact investigation and screening as well as TPT with 6 months of daily isoniazid (6H) for eligible children. However, coverage of TPT for eligible children below 5 years is low in both countries. WHO recently reported that only 24% and 15% of eligible children were initiated on TPT in 2018 in Cameroon and Uganda respectively [1].

### Description of the intervention

#### Facility-based model

This model implements a “passive” approach to the screening and management of household contacts (see definition in the “Study population” section) at the facility level as per current practice. Implementation follows current National Tuberculosis Program (NTP) recommendations, except that a 3-month regimen of daily rifampicin-isoniazid (3RH) as a fixed-dose combination (FDC) is offered as TPT to eligible child contacts. In the context of the study, sites also benefit from additional data collection and trainings with follow-up support for the facility staff.

When a person is diagnosed with bacteriologically confirmed pulmonary TB (index case), the facility staff in charge of TB (TB focal person) asks the index case to bring all household contacts with TB-related symptoms, all young (< 5 years) child contacts or older (5–14 years) child contacts living with HIV or exposed to HIV, irrespective of symptoms, to the health facility for evaluation for TB disease or for eligibility for TPT. This facility-based model is currently implemented in district hospitals in Cameroon for child contacts under 5 years old, but poorly applied for child contacts 5–14 living with HIV. In Uganda, the NTP allows household contact tracing when feasible but evaluation, TPT initiation, and follow-up are required to be done at the facility. In practice, due to lack of transport, the household contact tracing was poorly implemented. In both countries, at facility, TB investigations include clinical examination, sample collection for smear microscopy or Xpert MTB/RIF testing, and CXR when available and indicated, i.e., Xpert is negative or not done. Any contact diagnosed with TB is commenced on TB treatment, registered, and provided with treatment support and follow-up as per NTP guidelines. All sites are supported by the CaP TB program reducing the risk of heterogeneity of diagnosis and treatment of pediatric TB between sites and the two countries. Asymptomatic children who are eligible to receive TPT as 3RH (or 6H if drug-drug interactions with antiretroviral therapy preclude the use of rifampicin) are initiated at the facility with monthly follow-up (Fig. 1). The schedule of the facility-based model is presented in Table 2.

**Fig. 1 Fig1:**
[figure not shown]
Facility-based model flowchart

**Table 2 Tab2:** SPIRIT study schedule

	Baseline phase		Intervention phase								Evaluation phase
	Allocation*	Site assessment**	Enrolment of index cases	Enrolment of contact cases	Follow-up					End of study	
**Timepoint**			**-2 W**	**0**	***W1***	***W2***	***W4***	***W8***	***W12******	***W24***	
**Enrolment**											
**Eligibility screen**			X	X							
**Informed consent**			X	X							
**Allocation**	X										
**Interventions**											
**Facility-based arm**			X	X			X	X	X	X	
**Community-based arm**			X	X	X	X	X	X	X	X	
**Qualitative assessment**		X									X
**CEA**					X						
**Assessments**											
**Identification of contact children**			X								
**Children started on TPT**				X							
**Children completed TPT**									X	X	
**Acceptability of the intervention**		X									X
**TPT cost**					X						

*Abbreviations*: *W* week, *CEA* cost-effectiveness analysis, *TPT* TB preventive therapy

*Allocation takes place before the intervention begins as the clusters are randomized and not the individuals

**The baseline phase takes place 3 months before the intervention phase

***Children started on 6 months of isoniazid have 2 additional follow-up visits at week 16 and week 20

#### Community-based model

The intervention model is a decentralized, “active” approach to the screening and management of household contacts and is community-based. When an index case is diagnosed with bacteriologically confirmed pulmonary TB, the TB focal person asks whether s/he has child contacts in the household, and if so, then asks whether s/he is willing to receive a team in his/her household for contact symptom screening. If they agree, then an appointment is made and a team comprising a trained community health worker (CHW) and a research assistant goes in the household to screen all contacts (children and adults). If the index case does not have contact children in their household, then s/he is not included in the study, but contact investigation is done under routine care by the TB focal person. During the contact screening visit, the contacts who present symptoms of TB are referred to the health facility for TB investigations. Those who are asymptomatic and eligible for TPT (i.e., < 5 years irrespective of HIV status or 5–14 years and living with HIV) receive another visit by the TB focal person or TB nurse to initiate 3RH (or 6H if drug-drug interactions with antiretroviral therapy preclude the use of rifampicin). The follow-up is done at the household by the CHW after 1 week, 2 weeks, and then monthly in order to rapidly identify the children who develop TB symptoms in the community. The CHW collects the TPT at the health facility before each household visit and brings the remaining pills and documents back to the facility after the visit. During the follow-up visits, the CHW repeats the TB symptom screening, assesses the child’s TPT tolerability and adherence, and assesses the presence of any critical sign. If the child presents critical danger signs, tolerability problems, or TB symptoms, s/he is immediately referred to the health facility for a clinician to consult them (Fig. 2). The schedule of the community-based model is presented in Table 2.

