### Cluster selection and randomization

The study clusters are health facilities supported by the CaP TB Program with TB diagnostic and treatment capacity after an initial assessment taking into consideration the number of bacteriological index cases identified from January to December 2018 (minimum of 50). Priority was given to rural, semi-rural, or semi-urban facilities as there is less population movement than in an urban setting with relatively easy access. In Cameroon, there were mainly district hospitals because TB diagnosis is mainly done at the secondary healthcare level, with ten clusters selected from two regions (Central and Littoral regions). In Uganda, as TB services are decentralized at the primary healthcare level, the ten clusters were primary health centers in four districts in the South West region, some with two facilities per cluster in order to reach the minimum of 50 index cases per year.

The randomization was stratified by country, and in each country, the 10 clusters have been allocated to one of the study models by a covariate-constrained randomization [30] taking into account the number of bacteriologically confirmed TB cases from that cluster the previous year. The randomization was performed by a statistician from the central research team 3 months prior to the start of inclusions. Participants, healthcare providers, study staff, and investigators are not blinded to the allocation of the health facilities.

The cluster list can be found in the Supplementary Material.

Criteria to discontinue the allocated intervention to a cluster are the absence of recruitment in a cluster for more than 2 months or if the NTP proposes a similar intervention that would bias the outcomes of the study.

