#### Process data

In the baseline phase, sites were assessed in terms of quality of data collection in the registers and specific practices that would require adjustments for study organization of those sites. During the implementation phase, recruitment logs are filled in by research assistants to document study screening and enrolment process with reasons of refusal.

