### Statistical analysis

#### Primary analysis

The denominator for the analysis of the primary endpoint is the number of child contacts < 5 years and HIV-infected 5–14 years declared by the index case at the facility during the inclusion visit. Since discrepancies can be expected between what is declared by the index case and what is observed during contact screening, a sensitivity analysis will be performed using as denominator the number of children < 5 years of age and HIV-infected children of 5–14 years of age identified during the screening. An additional sensitivity analysis will be performed including only participants that followed all study procedures (per-protocol approach) among the declared and then enrolled child contacts. Dropping out of the cascade of cares and potentially being lost to follow-up can be the consequence of the models of care under evaluation. Therefore, lost to follow-up will be kept in the primary outcome analysis. They will be removed from the sensitivity per-protocol analysis.

A generalized linear mixed model with a binomial distribution and logit link function will be used to perform individual-level analysis adjusting for clustering. The regression model will include the fixed effect of treatment assignation and country and one random-effect for the cluster. A degree-of-freedom correction will be applied (between-within method) to deal with the type I error inflation due to the small number of clusters. The primary analysis will focus on the difference between the two study arms adjusted for country, and a secondary analysis will add an adjustment for unbalanced factors (urban/rural, district size) identified in the baseline assessment. For the analysis of the secondary outcomes, a similar mixed model will be used with the same random effects and correction method, focusing on each endpoint of the cascade of care for initiation and completion of TPT and each endpoint of the cascade of care for TB detection. The same model will be applied for the sensitivity analyses.

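### Recruitment is unblinded and follows allocation, only the community arm raises a home visit at entry, and no planned analysis of the primary endpoint checks for differential entry

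*Protocol article*

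**What the plan says.** All references are to the protocol article.

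- **Allocation** (Cluster selection and randomization): "The randomization was performed by a statistician from the central research team 3 months prior to the start of inclusions".
- **Blinding**, as described in that same section, is absent at every level: "Participants, healthcare providers, study staff, and investigators are not blinded to the allocation of the health facilities".
- **Community arm at entry** (Community-based model): the focal person first asks about child contacts. If there are any, the focal person "asks whether s/he is willing to receive a team in his/her household for contact symptom screening". Only the outcome of a yes is then described: "If they agree, then an appointment is made". The only stated reason for non-inclusion is a lack of children: "If the index case does not have contact children in their household, then s/he is not included in the study".
- **Facility arm at entry** (Facility-based model): the focal person "asks the index case to bring all household contacts with TB-related symptoms", together with the young or HIV-affected child contacts whether or not they have symptoms. No willingness question comes first.
- **Eligibility** (Study population): index cases qualify on bacteriological confirmation, age, recent diagnosis and declaring child contacts. Accepting a visit is neither an inclusion nor an exclusion criterion.
- **Consent** (Informed consent): in both arms the focal person takes the index case's consent at the inclusion visit, after explaining the study procedures.
- **Primary denominator** (Primary analysis): "The denominator for the analysis of the primary endpoint is the number of child contacts < 5 years and HIV-infected 5–14 years declared". That declaration is the one made at the inclusion visit. Losses to follow-up stay in, because dropping out may result from the model of care.
- **Records** (Process data): "recruitment logs are filled in by research assistants to document study screening and enrolment process with reasons of refusal". Under Sample size calculation, research assistants check that every confirmed index case in the treatment register is screened for eligibility.

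**The concern.** When participants are recruited after their cluster's arm is known, the two arms can end up enrolling different kinds of household. One unblinded conversation settles both whether an index case is eligible (child contacts are declared) and which children form the denominator (those declared).

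That conversation differs by arm. A facility-arm index case who consents and then never brings the children stays in the analysis, and the children count as not completed. A community-arm index case who does not want a team at home learns of the visit at or around the point of entry. If the reaction is to refuse study consent, the children are never counted. The protocol foresees such reluctance: Table 1 lists fears and stigma about household visits among the acceptability endpoints, and Challenges names stigma as a potential barrier.

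Unwillingness to be visited is a way in which the community model can fail to deliver preventive therapy. If it acts before enrolment rather than after, the primary endpoint does not see it.

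**Working it through.** **1. What happens to a community-arm index case who does not want the visit**

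| Response | Does the text settle it? | Effect on primary denominator |
|---|---|---|
| Consents, declares children, later refuses the team | Yes, by Study population and Primary analysis | Children stay, counted as not completed |
| Declares children, says no to the willingness question | Not explicitly; only the yes branch is described | Stay if included, absent if not |
| Refuses study consent because of the visit | Yes, not enrolled | Children absent |

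The facility arm has no visit request, so the last two rows have no direct counterpart there, although its index cases can refuse consent for other reasons.

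**2. Do the planned sensitivity analyses help?** The first replaces declared children with children identified at screening. In the community arm that presupposes an accepted visit. The second is per-protocol among declared and then enrolled contacts who followed all procedures. Both narrow the set to households that took part more fully, so neither can reveal who was lost at entry.

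**3. The plan's own figure.** Inputs from Sample size calculation: 60% versus 70%, ICC 0.01, coefficient of variation 0.5, 1500 children; 20 clusters, so m = 75. Alpha is taken as two-sided 5%. The printed 0.05% would give about 29% power.

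- Design effect = 1 + ((1 + 0.5²) × 75 − 1) × 0.01 = 1.9275
- Effective number per arm = 750 / 1.9275 = 389
- Power = 83.4% (83.8% with minor variants of the formula), against a stated 85%

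The sample size is reproduced within 2 points and is not in question here.

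**4. Illustration of the bias.** Let d be the share of eligible children lost at entry in the community arm, q the completion rate those children would have had, and p the completion rate among all eligible children. Then

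observed rate = (p − d·q) / (1 − d)

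Take p = 60% in both arms (no true effect) and no loss in the facility arm. The documents give neither d nor q; both are assumptions.

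- d = 5%, q = 0: 0.60 / 0.95 = 63.2%
- d = 10%, q = 0: 0.60 / 0.90 = 66.7%
- d = 10%, q = 30%: (0.60 − 0.03) / 0.90 = 63.3%
- Whole target effect, q = 0: 0.60 / (1 − d) = 0.70 gives d = 14.3%

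| d | Observed rate, q = 0 | Spurious difference, q = 0 | Spurious difference, q = 30% | Chance of a false finding for the community arm, q = 0 |
|---|---|---|---|---|
| 2% | 61.2% | +1.2 | +0.6 | about 5% |
| 5% | 63.2% | +3.2 | +1.6 | about 15% |
| 10% | 66.7% | +6.7 | +3.3 | about 49% |
| 14.3% | 70.0% | +10.0 | +5.0 | about 83% |
| 20% | 75.0% | +15.0 | +7.5 | about 99% |

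The last column uses the design effect above with 750 children analysed per arm; the nominal figure is 2.5%. If q equals 60%, the difference is zero at every d.

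**5. If the facility arm also loses households.** With q = 0, 10% lost in the community arm and 5% in the facility arm gives 66.7 − 63.2 = +3.5 points. The reverse gives −3.5, and equal losses give zero.

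**The case against.** A reader might infer that community-arm index cases must accept a home visit to enter the trial, so that every decliner is dropped and that arm's rate is inflated. The document does not support this. Willingness to be visited is not an eligibility criterion, and agreement is a condition of the appointment, not of inclusion. The question about children already precedes the question about the visit, so declaring no children in order to avoid a visit is conjecture. The primary denominator, with its rule of keeping drop-outs, would count an included decliner's children as failures.

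Other points also weigh against a strong claim. All registered confirmed cases are screened under supervision, and refusals are logged. Register-based comparisons between the models and with the pre-intervention period are planned outside the enrolled set. Facility-arm index cases can refuse consent too, and the Background describes the burden of bringing children to a facility, so selection could act in either arm. The missing no branch may be shown in the community-based flowchart or in the full protocol, neither of which is available here.

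Most of this stands, and it rules out claiming a defined exclusion or a known direction. It does not close the consent-refusal route, which no denominator based on enrolled index cases can see. The register comparisons do not adjust the primary estimate, and the article describes no analytic use of the logs. Strengths and Limitations do not mention selective recruitment.

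**Conclusion.** The concern holds as a risk of differential recruitment that the primary analysis and its two sensitivity analyses do not check. It rests on three things the article states: recruitment follows allocation, recruiters and participants are unblinded, and only the community arm raises a home visit at entry. That some index cases would refuse consent because of the visit is an inference, though one the acceptability endpoints make plausible.

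The size is unknown. The illustrative +3.2 and +6.7 points at 5% and 10% loss require that losses occur in the community arm only and that none of the lost children would have completed. They halve if those children would complete at 30% and vanish if they would do as well as the rest. A bias towards the community arm is the likelier direction, but it is not certain. This is worth correcting; it does not show that the trial's result will be biased.

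**What to change.** 1. State in Community-based model and Primary analysis that willingness to be visited is not a condition of inclusion. Declared eligible children of consenting index cases who decline the visit stay in the primary denominator as not completed, unless completion is recorded at the facility. This follows the article's own reasoning for keeping drop-outs.
2. Use the same child-contact question in both arms and record the answer before the visit is raised. The community arm already has this order, so it only needs to be fixed as a common step.
3. From the existing recruitment logs and treatment registers, tabulate registered, eligible, refused (with reasons) and enrolled index cases by arm and cluster. A gap between arms in the share found eligible would also show differential declaration of children.
4. Add a sensitivity analysis of children completing preventive therapy per registered eligible index case, by arm.

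The cost is a few sentences, one table and one extra analysis from data already collected, with a possibly slightly less favourable community-arm rate. Enrolment began in October 2019, so item 2 can act only on later inclusions. Items 3 and 4 cover the whole recruitment period, and item 1 covers it as far as declared children were recorded for decliners.

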**Fig. 2 Fig2:**
[figure not shown]
Community-based model flowchart

### Study population

Bacteriologically confirmed (by smear microscopy, Xpert MTB/RIF, or TB loop-mediated isothermal amplification (TB-LAMP) assays) index cases, > 15 years old who have been diagnosed less than a month prior to inclusion and declaring child contacts in the study catchment area, are eligible. Exclusion criteria are known multi-drug resistance (MDR), the index case being a prisoner, or TB patients from an already screened household from the study.

Contacts sharing the same enclosed space for frequent or extended periods of time with the index case or having slept in the same bed during the last 3 months as per the WHO definition of a contact case [24] are eligible unless they are already on TPT or on TB treatment.

For the qualitative assessment, the study population is represented by key informants (facility managers, health staff, community health workers, and community leaders) and by male and female TB patients, who are parents/guardians.

### Cluster selection and randomization

The study clusters are health facilities supported by the CaP TB Program with TB diagnostic and treatment capacity after an initial assessment taking into consideration the number of bacteriological index cases identified from January to December 2018 (minimum of 50). Priority was given to rural, semi-rural, or semi-urban facilities as there is less population movement than in an urban setting with relatively easy access. In Cameroon, there were mainly district hospitals because TB diagnosis is mainly done at the secondary healthcare level, with ten clusters selected from two regions (Central and Littoral regions). In Uganda, as TB services are decentralized at the primary healthcare level, the ten clusters were primary health centers in four districts in the South West region, some with two facilities per cluster in order to reach the minimum of 50 index cases per year.

The randomization was stratified by country, and in each country, the 10 clusters have been allocated to one of the study models by a covariate-constrained randomization [30] taking into account the number of bacteriologically confirmed TB cases from that cluster the previous year. The randomization was performed by a statistician from the central research team 3 months prior to the start of inclusions. Participants, healthcare providers, study staff, and investigators are not blinded to the allocation of the health facilities.

The cluster list can be found in the Supplementary Material.

Criteria to discontinue the allocated intervention to a cluster are the absence of recruitment in a cluster for more than 2 months or if the NTP proposes a similar intervention that would bias the outcomes of the study.

